#### Dashboard Delivery

Electronic dashboards for each patient participant were updated nightly using an automated script and stored as HTML in a password-protected relational database. Code hosted on a web server behind the Johns Hopkins University firewall was used to retrieve and display dashboards to the clinicians treating patient participants. Multiple guardrails were in place to control access to patient participant dashboards by the treating clinicians. The clinicians were allotted permission in our study’s Microsoft Active Directory group and connected to the Johns Hopkins University virtual private network to access the dashboard’s landing page. Upon reaching the dashboard’s landing page, treating clinicians were prompted to authenticate themselves using Johns Hopkins single sign-on (with 2-factor authentication). A cookie generated by the single sign-on authentication procedure was used throughout the dashboard to ensure that clinicians could only access dashboards for their own patient participants. The list of appropriate patient participants (including a participant ID and name) was shown to the clinician to facilitate navigation around the dashboard.

#### Data Privacy

We worked closely with our technology team to implement several solutions that helped preserve the privacy of the data collected through the Bark app. We developed a coding system for patients to log into the Bark app so that Bark would not have direct access to any personally identifying information about the patients who were under our care and participating in the study. In addition, we transferred and processed all the collected data to servers behind the Johns Hopkins University firewall that could only be accessed by approved study team members using Johns Hopkins University’s standard 2-factor authentication procedures. To further protect the privacy of the data collected through the app, we implemented a pipeline that minimized manual review of the data to only what was necessary to process the data and use it clinically. In addition, we instructed clinicians to review the appropriate dashboards only when they met with their patients, and at that time they could address any potential concerns that emerged from the collected data. We informed patients that the collected data would not be monitored in real time, so they were aware of the procedures.

### Randomized Trial

#### Overview

Motivated by our conceptual model, we hypothesized that providing clinicians with an electronic dashboard of their patients’ digital social activity before routine clinical encounters would aid the dialogue and exchange of relevant collateral information during those encounters and thereby improve patient outcomes. The goal was to test this hypothesis in a randomized pragmatic trial comparing patients who received care augmented by the electronic dashboard versus patients who received TAU. The primary research questions to be addressed by the trial were as follows: (1) Is the use of the electronic dashboard in routine care feasible and acceptable to both patients and their clinicians? and (2) Does the use of the electronic dashboard in routine care improve outcomes for patients with depression or anxiety disorders? The outcomes to be examined are described subsequently.

#### Study Sample

The study was carried out in outpatient psychiatry clinics across the Johns Hopkins Medical Institution and the Kennedy Krieger Institute, which is affiliated with but separate from the Johns Hopkins Medical Institution. We focused on clinics that use a collaborative care model in which patients see a psychiatrist for medication-assisted care as well as a master’s level therapist or doctoral-level psychologist for ongoing psychotherapy. Both clinicians and patients were recruited to participate in the study. We first recruited clinicians in the selected clinics to participate in the study and then sought to enroll patients on their case rolls. Patients aged ≥12 years with a mood or anxiety disorder receiving ongoing care were eligible. To be pragmatic and stay as close to the real world as possible, there were no exclusion criteria other than if the treating clinician determined the patient was not able to provide informed consent. In addition, all patients who met the inclusion criteria were eligible, regardless of their current mental health status and scores on patient or clinician rating scales.

#### Study Procedures

All patient participants downloaded the Bark app and went through the process of connecting their social media and electronic communication platforms to the app. To promote trust and participation in the study, we allowed patients to decide which platforms to connect to the Bark app. While patients retained final control of the decision, we explained to them that their most frequently used apps would provide the most relevant information. Patients were randomized within strata formed by treating clinicians in a 1:1 ratio with blocks of size 2 to either the dashboard intervention or TAU. The purpose of stratified randomization in blocks was to promote balance in the number of patient participants in the 2 treatment arms seen by each clinician, thereby reducing the impact of differences between treating clinicians on comparisons of patient outcomes between the 2 arms. For patients in the intervention arm, the electronic dashboard was delivered to the treating clinician before scheduled clinical visits. The clinician and patient collaboratively decided when and how to use the dashboard in the session during each clinical encounter. For patients in the TAU arm, the clinician did not receive a clinical dashboard for review. After the initial visit to download the Bark app, there were no more study-specific research visits. To be pragmatic and stay as close to the real-world setting as possible, patients continued to be seen by their clinician as clinically indicated. The first regularly scheduled clinic visit with their clinician after the patient consented and downloaded the Bark app was considered the study’s baseline visit. Patients were then followed through their clinical care for up to 6 months, and all study measures were completed during their regularly scheduled clinic visits.

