### Ethical Considerations

The study protocol was approved by the Johns Hopkins University School of Medicine Institutional Review Board (#00184638). We obtained informed consent from both patients and clinicians who participated in the study, ensuring voluntary participation and understanding of objectives, procedures, and potential risks of the study. We obtained assent from patients who were aged <18 years and consent from their guardians. All personal data collected were anonymized and stored in encrypted electronic databases, accessible only to the research team members. To compensate participants for their time and effort, patients received US $100 at randomization and another US $100 at the completion of the study. Participants who shared iOS text data were compensated US $50 because of the extra work required from the participants to share these data. Therapists received US $100 for enrolling 5 patients, US $200 for enrolling 10 patients, and US $250 for enrolling ≥15 patients.

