## Results

The study was initiated in April 2019, but progress was delayed due to the onset of the COVID-19 pandemic. Data collection has been completed, and the study results will be reported in a separate manuscript. The study is registered on ClinicalTrials.gov (NCT03925038).

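### Blocks of 2 within each unblinded clinician make the second allocation of each pair deducible, and the primary model commits to no baseline adjustment that would limit the resulting bias

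*Protocol article*

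**What the plan says.** Study Procedures fixes the allocation: "Patients were randomized within strata formed by treating clinicians in a 1:1 ratio with blocks of size 2". The reason given is balance between the arms within each clinician. The same section makes the arm visible to the clinician: "For patients in the intervention arm, the electronic dashboard was delivered to the treating clinician before scheduled clinical visits", whereas "For patients in the TAU arm, the clinician did not receive a clinical dashboard for review".

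Study Sample describes where patients come from: "We first recruited clinicians in the selected clinics to participate in the study and then sought to enroll patients on their case rolls". It also says that "there were no exclusion criteria other than if the treating clinician determined the patient was not able to provide informed consent", and that patients enter whatever their current symptom scores. Ethical Considerations adds that "Therapists received US $100 for enrolling 5 patients", with larger sums for 10 and for 15 or more.

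Statistical Analysis commits to fixed effects for arm and time, patient random effects, and clinician random effects if indicated. The primary test is the treatment term. Demographics, diagnosis and number of visits are only to be considered as covariates. Baseline PHQ-9 is not among the examples, and a treatment-by-time interaction is only a possibility.

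Results reports the stage reached: "Data collection has been completed, and the study results will be reported in a separate manuscript".

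**The concern.** In a 1:1 block of 2, the first allocation fixes the second. Here the stratum is one clinician, and that clinician learns the arms. Concealing the list centrally does not prevent the deduction, because it rests on an arm already seen. If a clinician had any influence over which patient came next, a patient could be matched to a slot whose arm was already clear. Entry at any level of severity leaves wide room for such patients to differ.

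The committed model would pass this imbalance on. The treatment main effect averages scores over follow-up, so a difference present at entry is counted as a treatment difference. A clinician random effect does not help, because the imbalance arises between patients of the same clinician. Limitations does mention selection bias, but it concerns who takes part and what they share, not predictable allocation.

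**Working it through.** **Inputs from the article:** N = 100, at least 3 repeated measures, target d = 0.5, 80% power (Sample Size); significance threshold 0.05 (Statistical Analysis), taken as two-sided; block size 2 (Study Procedures).

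**Assumptions, not in the article:** 10 to 30 clinicians; correlation ρ = 0.6 between repeated scores (range 0.5–0.7); a gap g of 0.3 or 0.5 SD between patients in known dashboard slots and known TAU slots; every determined slot exploited.

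**1. The plan's own figure.** The mean of three equally correlated measures has variance (1 + 2ρ)/3, so SE = √[(4/100)(1 + 2ρ)/3]. At ρ = 0.6 this is √(0.04 × 0.733) = 0.171, and power for d = 0.5 is 83%. At ρ = 0.5 power is 86.5%, and at ρ = 0.7 it is 79.8%. Exactly 80% needs ρ = 0.694. The stated power is therefore attainable and is not in dispute.

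**2. Share of determined allocations.** A clinician with n patients has floor(n/2) determined allocations: 2/5 = 40% for 5 patients, 5/10 = 50% for 10, 7/15 = 47% for 15. If about half of C clinicians end on an odd number, the overall share is s = (100 − C/2)/200:
- C = 10: 95/200 = 0.475
- C = 20: 90/200 = 0.450
- C = 30: 85/200 = 0.425
- complete blocks throughout: 0.50

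**3. Bias and type I error, no true effect.** Bias = s × g. Type I error = Φ(bias/SE − 1.96) + Φ(−bias/SE − 1.96), with SE = 0.171.

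| g | s | Bias (SD) | Type I error |
|---|---|---|---|
| 0.3 | 0.425 | 0.128 | 12% |
| 0.3 | 0.475 | 0.143 | 13% |
| 0.3 | 0.50 | 0.150 | 14% |
| 0.5 | 0.425 | 0.213 | 24% |
| 0.5 | 0.475 | 0.238 | 28% |
| 0.5 | 0.50 | 0.250 | 31% |

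Over ρ = 0.5 to 0.7 the type I error ranges are 11–15% for g = 0.3 and 22–33% for g = 0.5.

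**4. What baseline adjustment does.** If selection acts on the stable part of the PHQ-9 score, adjustment leaves about a fraction (1 − ρ) of the bias. In a simulation with g = 0.4 and complete blocks, bias fell from about 0.20 to 0.10 SD (ρ = 0.5) or 0.06 SD (ρ = 0.7). Type I error fell from 20–23% to 8–11%. This agrees with 0.20 × 0.5 = 0.10 and 0.20 × 0.3 = 0.06. Selection on something unrelated to baseline PHQ-9 would not be reduced.

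**5. Form of the check.** Let known dashboard slots hold patients shifted by −g/2 and known TAU slots patients shifted by +g/2. Pooling all second-in-block patients gives an average shift of zero, whereas the contrast by predicted arm gives g. In simulation with g = 0.5, the pooled first-versus-second contrast averaged about 0.00 and the contrast by arm recovered 0.50.

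**6. Precision of the check and of the supportive estimate, complete blocks.** The baseline contrast among second-in-block patients has about 25 per arm: SE = √(2/25) = 0.28 SD, so 80% power needs a gap of about 2.80 × 0.283 = 0.79 SD. The first-in-block estimate has SE = √[(4/50) × 0.733] = 0.24 SD, so 80% power needs an effect of about 2.80 × 0.242 = 0.68 SD.

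**The case against.** A reader might infer that half the allocations were known to clinicians in advance. The article does not support that. It does not say that clinicians were told the block size, or when they learned one patient's arm relative to the next enrolment. The arm shows when a dashboard does or does not arrive before a scheduled visit, so patients enrolled close together may have been allocated before either arm was visible. The shares above are therefore upper bounds. Concealment details may also stand in the full protocol, which is not shown.

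Clinicians' influence over enrolment is partly inferred. The article describes the study team seeking patients on clinicians' case rolls, and the clinician's exclusion covers only capacity to consent. Payment for enrolling implies some role, but it depends on the number enrolled and not on the arm, so it gives no motive to steer by severity.

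Nor can it be said that the analysis could not reveal or reduce the problem. Baseline PHQ-9 is collected, the covariate list is open-ended, and a treatment-by-time interaction is contemplated.

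These objections narrow the point without removing it. The pairing and the open arms are stated, the deduction follows from them, and none of the possible safeguards is committed to.

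**Conclusion.** The point holds in conditional form. The design lets a clinician who knows or infers the pairing deduce up to about 43–47% of allocations (50% with complete blocks), and the primary model has no committed protection against selection on that knowledge. With full exploitation and an assumed gap of 0.3 to 0.5 SD, bias would be about 0.13–0.25 SD, at most half the target effect of 0.5. Type I error would be about 12–31% in place of 5%. Gap, correlation, number of clinicians and degree of exploitation are all assumptions. Nothing in the article shows that selection took place, and these figures should not be read as an estimate of the bias in this trial. Allocation can no longer be changed, but the analysis and the reporting can.

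**What to change.** Before results are reported:

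1. Commit to adjusting the primary model for baseline PHQ-9, entered as a covariate and not also kept as a post-treatment outcome. The score is already collected, and patients complete it before the visit. This reduces the bias but does not remove it. If baseline was counted among the three measures, two remain as outcomes.
2. Add a Berger-Exner check by predicted arm, using the existing randomisation list. Compare baseline PHQ-9 between second-in-block patients forced to dashboard and those forced to TAU. Then test each patient's prior probability of dashboard allocation (0, 0.5 or 1) as a predictor of outcome within arm. Do not pool second-in-block patients across arms, since opposite selection would cancel and falsely reassure. Given its low power, report the contrast with a confidence interval and do not treat a non-significant result as proof of no selection.
3. Report an estimate from first-in-block patients only, whose arm could not be deduced from the block. It uses about half the patients (SE about 0.24 SD), so it is supportive only.
4. State the predictability as a limitation, with whatever is known about whether clinicians knew the block size and when they learned each arm.

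The cost is a few lines of analysis and a short paragraph; no new data are needed.

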#### Study Measures

Both the patient and clinician participants completed measures throughout the study follow-up. The measures were selected to address the primary research questions and (based on our conceptual model) to tap into potential mediating constructs. Table 1 provides the schedule of measures during the study follow-up.

**Table 1 table1:** Schedule of participant measures.

Measures		Baseline	Every clinic visit	Every 3 months^a^
**Patient and clinician**				
	Consent	✓		
	Demographics	✓		
**Patient**				
	CSQ^b^	✓		✓
	SF-36 MHC^c^	✓		✓
	WAI-SR^d^	✓		✓
	SES^e^		✓	
	PHQ-9^f^ and GAD-7^g^		✓	
	Patient questionnaire			✓
**Clinician**				
	MFAS^h^	✓		
	M-CICAS^i^		✓	
	EDMH^j^		✓	
	WAI-SRT^k^	✓		✓
	Clinician questionnaire			✓

^a^These measures were collected every 3 months, coinciding with the nearest regularly scheduled clinic visit.

^b^CSQ: Client Satisfaction Questionnaire.

^c^SF-36 MHC: 36-Item Short Form Health Survey Mental Health Component.

^d^WAI-SR: Working Alliance Inventory-Short Revised.

^e^SES: Session Experience Scale.

^f^PHQ-9: Patient Health Questionnaire-9.

^g^GAD-7: Generalized Anxiety Disorder-7.

^h^MFAS: Monitoring and Feedback Attitudes Scale.

^i^M-CICAS: McLean Collateral Information and Clinical Actionability Scale.

^j^EDMH: Electronic Data and Mental Health.

^k^WAI-SRT: Working Alliance Inventory-Short Revised-Therapist.

#### Patient Measures

To measure proximal outcomes on mental health symptoms, participants completed the Patient Health Questionnaire-9 (PHQ-9) [58] and Generalized Anxiety Disorder-7 (GAD-7) [59] at the baseline and every subsequent clinic visit during follow-up. The PHQ-9 is a 9-item measure of current depressive symptoms ranging from 0 to 27, with higher scores representing greater levels of depression. The GAD-7 is a 7-item measure of current anxiety symptoms that ranges from 0 to 21, with higher scores representing greater levels of anxiety. In addition, to measure more distal outcomes on overall mental health–related quality of life, participants completed the Short Form-36 Health Survey Mental Health Component (SF-36 MHC) at baseline and every 3 months, coinciding with their nearest regularly scheduled clinic visit. This 13-item mental health component scoring ranges from 0 to 100, with higher scores indicating higher mental health–related quality of life [60]. We selected these measures as our primary (PHQ-9) and secondary (GAD-7 and SF-36 MHC) outcomes because they are brief, making them pragmatic to collect, and they are widely used with well-established psychometric properties for measuring important clinical outcomes that, based on the conceptual model we hypothesized, will improve with the proposed intervention.

To measure the overlapping constructs of therapeutic alliance and patient satisfaction, participants completed the Working Alliance Inventory-Short Revised (WAI-SR) and Client Satisfaction Questionnaire at baseline and every 3 months, coinciding with their nearest regularly scheduled clinic visit. The WAI-SR is a 12-item measure of the goal, task, and bond aspects of the therapeutic alliance, and each item ranges from 1 to 5, with higher scores indicating greater alliance [61]. The Client Satisfaction Questionnaire is an abbreviated 8-item measure of patient satisfaction with clinical therapy sessions, and each item ranges from 1 to 4, with higher scores reflecting greater satisfaction [62]. In addition, to further measure therapeutic alliance after every clinic visit, patients completed the Session Experience Scale. This is a 4-item scale that assesses key dimensions of effective therapeutic relationships [63]. Finally, at the end of the study follow-up, patients completed the patient questionnaire, which was a 4-item open-ended measure of the patient-clinician relationship that we developed to assess patient perception of the therapeutic relationship with their clinician and whether discussions about electronic communication had occurred and whether this was helpful.

#### Clinician Measures

At baseline, clinicians completed the Monitoring and Feedback Attitudes Scale. This is an 18-item measure of clinician attitudes toward treatment tracking and the usefulness of incorporating individualized progress measures. It is scored on a 5-point Likert scale, with higher scores indicating more positive attitudes [64]. To measure clinician perspectives on the therapeutic alliance, they completed the WAI-SR-Therapist at baseline and every 3 months, coinciding with the patient’s nearest regularly scheduled clinic visit. This is a 10-item version of the WAI-SR, and each item is rated on a 0 to 5 scale, where higher scores represent a higher alliance [65]. In addition, at every clinic visit, clinicians completed the McLean Collateral Information and Clinical Actionability Scale (M-CICAS) and the Electronic Data and Mental Health (EDMH) Questionnaire. The M-CICAS [66] collects information on the collateral sources of information reviewed, clinical actions taken, and shared decisions made between a clinician and a patient in a clinical session. The EDMH Questionnaire is a 6-item assessment of electronic communication that was completed by clinicians after sessions with patients randomized to the dashboard arm. It includes three Likert-rated questions: (1) Did review of electronic communications affect topics discussed in sessions? (2) How helpful was the review of this information to patient care? and (3) How likely is the clinician to recommend reviewing electronic communication to other clinicians? The questionnaire also includes 3 open-ended questions to gather more context about responses to the first 3 questions. Finally, at the end of the study, clinicians completed the clinician questionnaire, which is a 2-item open-ended survey to measure the use of dashboard-prompted electronic communication in discussion and the usefulness of the dashboard on patient care. We developed the EDMH Questionnaire and clinician questionnaire, but these have not been validated. They were included to gather additional qualitative data on the experience of using the dashboard in clinical care for exploratory analyses.

#### Data Management

The PHQ-9 and GAD-7 were collected as part of an MBC program that has been implemented in our clinics. As part of this program, patients completed the PHQ-9 and GAD-7 before every clinic visit through the Epic electronic health record as part of routine care. All other measures were collected remotely at the scheduled times via text with a link to questionnaire forms developed in a REDCap (Research Electronic Data Capture; Vanderbilt University) database that is maintained by approved study team members at Johns Hopkins University. These data are to be joined and processed for downstream analyses after removing all patient identifiers except for dates of service.

#### Statistical Analysis

The primary outcome of the trial is the difference in depressive symptoms measured by the PHQ-9 total score over the course of follow-up between the dashboard intervention and TAU arms. Secondary outcomes include differences in anxiety symptoms measured by the GAD-7 total score and in the more distal outcome of functioning, as measured by the SF-36 MHC. Because the PHQ-9 and GAD-7 were collected at each clinic visit and the SF-36 MHC at baseline and end of the study, there are repeated measures over time for each scale within individual patients. We plan to use random effects linear regression models to test for differences in scores on these measures between the 2 treatment arms. We will include fixed effects terms for the treatment arm as well as for time. Furthermore, we will consider including fixed effects terms for potential confounders, such as demographics (eg, age, sex, and race), and clinical factors, such as primary diagnosis and the number of clinic visits as an indicator of clinical severity. We will also include random effects for individuals to account for the correlation in outcome measures within repeated measures of the same individual as well as for clinicians, if indicated, to account for the potential clustering effects of treatment within clinicians. The primary statistical test of interest will focus on the fixed effects term for treatment, which will provide an estimate of the mean differences in the outcome measures between the 2 treatment arms, controlling for time. We will consider different functional forms of the time covariate and use the one that provides the best fit to the data on changes in score over time. Given that patients will be enrolled in the study regardless of their current mental health status and scores on these outcome measures, we consider the model in which we control for time to be the most appropriate test of differences between the treatment arms. However, we may consider examining interactions between treatment and time to see whether changes in the scores over time differ between the 2 treatment arms. We will use the conventional threshold of *P*<.05 to declare differences statistically significant.

In additional exploratory analyses, we will examine whether there are differences between the 2 treatment arms in measures of therapeutic alliance and detection of clinically actionable targets, both of which we hypothesize, based on our conceptual model, may mediate the therapeutic effect of the intervention. These analyses will provide important evidence as to whether the proposed intervention actually engages the targeted mechanisms of action. In particular, we will test whether there are differences between the 2 treatment arms on scores on the WAI-SR (which measures therapeutic alliance for both patients and clinicians) and the M-CICAS (which captures information about the detection of clinically actionable targets and whether subsequent treatment adjustments were made). For the WAI-SR score, which is a quantitative measure and was captured every 3 months, we will use the same modeling approach as statistical modeling for the primary and secondary outcomes. For the M-CICAS, which was captured after every clinic visit, we will tally the number of times issues related to the patient’s social media activity or electronic communications were discussed in the clinical encounter and the number of times treatment adjustments were made. We will again use the same modeling approach as described earlier, except that we will use random effects logistic regression models to carry out separate tests of differences in the probability of these events occurring over time between the 2 treatment arms. Furthermore, we will use *P*<.05 as the threshold to declare findings significant even though multiple tests will be carried out because these analyses will be exploratory.

Finally, we will conduct a series of analyses to assess the feasibility and acceptability of the intervention. We will use several different approaches to do this. First, we will provide descriptive statistics on how many clinicians and patients whom we approached agreed to participate and the reasons why some declined. We are particularly interested in learning whether clinicians and patients decline due to concerns about privacy in sharing personal information obtained from their social media and electronic communication activity or due to the burden of collecting and sharing this information during busy clinical encounters. Second, we will examine descriptive statistics regarding which social media and electronic communications platforms patients agreed to share to assess whether patients were selective about what information they voluntarily provided. Third, we collected a qualitative survey from clinicians to describe the main themes on whether they found systematically discussing social media and electronic communications during treatment helpful, and, if so, what they found most useful.

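### SF-36 MHC has two conflicting collection schedules, and separately its planned arm main effect, with baseline counted as an outcome, keeps only about a third to two thirds of the end-of-study difference

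*Protocol article*

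**What the plan says.** On timing, Patient Measures has participants completing the "Short Form-36 Health Survey Mental Health Component (SF-36 MHC) at baseline and every 3 months". Table 1 ticks SF-36 MHC at baseline and in the 3-monthly column, and its footnote a reads "These measures were collected every 3 months, coinciding with the nearest regularly scheduled clinic visit". Study Procedures adds "Patients were then followed through their clinical care for up to 6 months". Together these imply waves near months 0, 3 and 6. Statistical Analysis instead gives "the SF-36 MHC at baseline and end of the study".

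On the model, the same sentence of Statistical Analysis concludes that "there are repeated measures over time for each scale within individual patients". For SF-36 MHC as described there, this can be true only if baseline is itself one of the outcomes. The planned model is a random-effects linear regression with fixed effects for arm and time. "The primary statistical test of interest will focus on the fixed effects term for treatment", controlling for time. The alternative is optional: "we may consider examining interactions between treatment and time". The covariates named as possible are demographics, primary diagnosis and number of visits. Baseline SF-36 MHC is not among them.

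**The concern.** There are two separate problems.

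The first is a contradiction about which SF-36 MHC scores exist. WAI-SR has the same ticks in Table 1, and the analysis section describes it as captured every 3 months, so two measures on one schedule are given different timings. Data collection is complete and results are not yet reported. Until the text is reconciled, a reader cannot tell whether the planned analysis has two waves or three.

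The second concerns what is estimated. Randomisation makes the expected arm difference at baseline zero. If the baseline score is an outcome and one common arm effect is fitted across all waves, that zero is averaged in with the later differences. The tested coefficient is then smaller than the end-of-study difference, and the test loses power. SF-36 MHC is the only functioning measure among the primary and secondary outcomes, so a null result on it could be misread as evidence of no benefit.

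**Working it through.** **The plan's own figure.** Sample Size gives 80% power for the primary outcome at d = 0.5, with 100 patients and at least 3 measures. No figure is given for SF-36 MHC. One measure with 50 per arm gives about 70%. The mean of three measures, all carrying the full 0.5, gives 80% at a correlation of about 0.69 (normal approximation). The 80% is attainable for PHQ-9 under that unstated correlation, and nothing below contradicts it.

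**Inputs for SF-36 MHC.** From the article: 100 patients, 1:1 allocation (50 per arm) and a 0.05 threshold, taken as two-sided. Assumed: end-of-study difference 0.5 SD (borrowed from Sample Size), no arm difference at baseline, equal correlation r between waves, unit SD, random intercept per patient, complete data. Power is from the noncentral t with 98 degrees of freedom and SE = √(2v/50), where v is the variance per patient.

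**Step 1: what the arm term estimates.** With complete data it is the arm difference in patient means over the m waves.
- Two waves: (0 + 0.5)/2 = 0.25, a share of 0.50.
- Three waves, linear growth: (0 + 0.25 + 0.5)/3 = 0.25, a share of 0.50.
- Three waves, full effect by month 3: (0 + 0.5 + 0.5)/3 = 0.33, a share of 0.67.
- Three waves, effect only after month 3: (0 + 0 + 0.5)/3 = 0.17, a share of 0.33.

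Categorical and linear time give the same shares. If 20% of patients have only a baseline score, the two-wave share falls to 0.41–0.43 for r from 0.7 to 0.3.

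**Step 2: variances.**
- Main effect over m waves: v = (1 + (m−1)r)/m.
- End score adjusted for baseline: v = 1 − r².
- Mean of months 3 and 6 adjusted for baseline: v = (1 + r)/2 − r².

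At r = 0.5 the first two compare directly. Two-wave main effect: v = 0.75, SE = √(1.5/50) = 0.173, ratio 0.25/0.173 = 1.44. Baseline-adjusted end score: v = 0.75, the same SE, ratio 0.5/0.173 = 2.89. The standard error is unchanged and the signal is halved.

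**Step 3: power.**

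| Analysis | r = 0.5 | r = 0.6 | r = 0.7 |
|---|---|---|---|
| Main effect, months 0 and 6 | 30% | 28% | 27% |
| Main effect, months 0, 3, 6, linear growth | 33% | 30% | 28% |
| Main effect, months 0, 3, 6, full by month 3 | 52% | 49% | 45% |
| End score, baseline as covariate | 82% | 87% | 93% |
| Mean of months 3 and 6, baseline as covariate, full by month 3 | 94% | 96% | 98% |
| Same, linear growth | 75% | 80% | 87% |
| Same, effect only after month 3 | 42% | 46% | 54% |

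At r = 0.3 the first and fourth rows are 34% and 74%.

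**Reading the table.** Adding month 3 while keeping the planned model changes little under linear growth (30% to 33% at r = 0.5). Most of the gain comes from moving baseline out of the outcomes. Averaging months 3 and 6 is best only if the effect is early; under linear growth or a late effect, the end-of-study contrast is stronger.

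**The case against.** A reader might infer that the analysis discards the month-3 scores and that this omission causes the halving. The article supports neither step. Statistical Analysis misdescribes the collection but states no rule excluding a wave, and a random-effects model accepts every available score. The same modelling approach is planned for WAI-SR, acknowledged there as 3-monthly. The article is also loose with these terms elsewhere: Table 1 places the patient and clinician questionnaires in the 3-monthly column, while the text places them at the end of follow-up or of the study. Loose wording is the likelier explanation. Step 1 shows that the dilution persists with month 3 restored.

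It is also fair to say that SF-36 MHC is a secondary outcome, that no power was claimed for it, and that an article commonly leaves baseline adjustment to the full analysis plan. The authors give a reason for testing the main effect: patients enter regardless of current score. The optional treatment-by-time term would recover the full difference.

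These points limit the finding but do not remove it. The article does more than stay silent: it counts baseline as a repeated outcome, names the arm main effect as the test and leaves the interaction optional. Variation in entry scores is a reason to adjust for baseline, not to average it into the outcome.

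**Conclusion.** Both defects stand, independently of each other. The SF-36 MHC timing in Statistical Analysis contradicts Patient Measures and Table 1; which is right cannot be settled from the article. The model as described tests a diluted quantity: half of the end-of-study difference with two waves, and one third to two thirds with three. In the two-wave case power is 27–30%, against 82–93% for the baseline-adjusted end score, at correlations of 0.5 to 0.7.

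The shares rest on no baseline difference, complete data and a random intercept. The power figures also rest on the assumed 0.5 SD difference and correlations. The 94–98% for months 3 and 6 combined should not be quoted alone, because it needs the full effect by month 3. The Conceptual Model treats functioning as a distal outcome that follows symptom change, so a later effect is plausible. This is a should-fix point on a secondary outcome.

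**What to change.** 1. State the SF-36 MHC waves identically in Statistical Analysis, Patient Measures and Table 1, according to what was actually collected.
2. Take baseline SF-36 MHC out of the outcome vector and enter it as a covariate.
3. If month-3 scores exist, model all post-baseline waves with arm by categorical time and test the arm contrast at end of study. With complete data and the assumptions above, its power is that of the baseline-adjusted end score, whenever the effect appears.
4. If only the end score exists, analyse it adjusted for baseline.

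The cost is a wording correction and a small amount of analysis work, using scores already collected. The choice should be fixed and dated before arm-level SF-36 MHC results are examined.
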